#### Nutritional status data

2.4.2

(1)Nutritional status assessment: nutritional risk screening 2002^[34]^ (the ESPEN endorsed screening tool based on BMI, weight loss and appetite as well as acute illness)^[2]^(2)Nutrition therapy monitoring data: initiate time of EN, feeding amount, response to feeding, albumin, pre-albumin, total lymphocyte count, glucose, electrolytes (potassium, magnesium, phosphate)

### 16S rRNA sequencing and analysis of structure and composition of gut microbiota

2.5

#### Feces collection and preservation

2.5.1

Fecal samples will be collected on admission and days 3 and 7. For patients hospitalized in the ICU for longer than 14 days, an additional fecal sample will be collected on day 14. All fecal samples will be collected by inserting a sterile rectal swab into the anus 1 to 2 cm and rotating the swab 3 to 4 times. The swabs will be placed in a sterile Eppendorf tube and immediately stored in a refrigerator at −80°C until use.

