**Methods::**

One hundred ICU patients with trauma or in a period of acute stress after surgery will be enrolled, and their fecal samples will be collected at different timepoints for microbial sequencing and analysis. General clinical data (demographic information, surgical data, laboratory parameters, illness severity scores, and therapeutic drugs), nutritional status data (nutritional status assessment and nutrition therapy monitoring data), as well as clinical outcomes, will be recorded. The microbial and clinical data will be combined to analyze the baseline characteristics and dynamic alterations of gut microbiota along with the incidence of EN intolerance. Data related to the gut microbiota will be statistically analyzed by R software, and other data performed by SPSS23.0 software.

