## Introduction

1

Nutritional status is an important factor that directly affects the outcome of intensive care unit (ICU) patients and is closely related to the survival of ICU patients.^[1]^ At present, nutritional supportive approaches used in clinical practice include enteral nutrition (EN) and parenteral nutrition,^[2]^ and the former has advantages in maintaining the integrity of the intestinal barrier, preventing intestinal bacterial translocation, and reducing enterogenous infection. In addition, EN is more fit in with human physiology than parenteral nutrition and plays an irreplaceable role in the secretion and motility functions of the gastrointestinal tract.^[3–5]^

Early EN is widely accepted and used in the field of critical care medicine. However, for ICU patients, the implementation of EN is accompanied by great risks and challenges. The incidence rate of EN intolerance is very high. Severe trauma, shock, and postoperative critical patients are difficult to tolerate EN, and very few even occur nonobstructive intestinal necrosis. Retrospective analysis of nutrition practice data from 1888 patients in 167 ICUs worldwide found that the incidence rate of interruption of feeding due to EN intolerance was as high as 30.5% (576/1888), and clinical symptoms of EN intolerance appeared on average within 3 days (range: 1–12 days).^[6]^ For ICU patients, the need for nutrition is urgent, and if the application of EN is blocked due to intolerance, it will cause a second hit to the patients and hurt the prognosis of the patients. Therefore, it is an urgent task to reveal the causes of EN intolerance in ICU patients under stress state and to find effective treatment methods.

Although many researchers have tried to explore the causes of EN intolerance from the demographic or clinical characteristics, no appropriate laboratory or clinical indicators have been found to guide the nutritional supportive treatment.^[7–12]^ Gungabissoon U et al^[6]^ conducted demographic statistics on patients with EN tolerance and intolerance in ICU, and found that there were no statistical differences in age, gender, body mass index (BMI), and disease severity between the 2 groups. Lavrentieva A et al^[13]^ also found that there were no statistical differences in age, sex, burn index, burn area percentage, Acute Physiology, and Chronic Health Evaluation II score and sequential organ failure assessment score between septic burn patients with EN tolerance and intolerance.

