### Study aim

2.1

The study aims to observe the effect of EN on the gut microbiota of ICU patients, and screen microbiological markers for predicting EN intolerance in ICU patients.

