#### General clinical data

2.4.1

(1)Demographic information: ID, sex, age, weight (kg), height (cm), BMI calculation (kg/m^2^), comorbidities, smoking history, drinking history, medication history(2)Surgical data: clinical diagnosis, surgical site, operative time, the amount of intraoperative blood loss and blood transfusion, intraoperative hypotension (mean arterial pressure <65 mm Hg) duration(3)Laboratory parameters: blood count, platelet count, lymphocyte ratio, creatinine, liver tests (aspartate aminotransferase, alanine aminotransferase, gamma-glutamyl transferase, alkaline phosphatase), bilirubin(4)Illness severity scores: Glasgow, Acute Physiology, and Chronic Health Evaluation II, and sequential organ failure assessment(5)Therapeutic drugs: proton pump inhibitors, prokinetics, gastric mucosal protectors, coagulants, anticoagulants, antibiotics, vasopressors, anti-diarrhea medicine, cathartics, probiotics(6)Clinical outcomes: duration of mechanical ventilation, length of ICU stay, length of hospital stay, mortality, infections

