In recent years, researchers have proposed that particular gut microbiota signatures could be used to predict the occurrence, development, or clinical outcomes of certain diseases. Agudelo-Ochoa et al^[38]^ found that the gut microbiota of ICU patients with sepsis has an increased abundance of microbes tightly associated with inflammation and the abundance of pathogenic species, such as *Enterococcus spp*., was differentially increased in sepsis patients who died. Reitmeier et al^[39]^ demonstrated in 1976 subjects of a German population cohort (KORA, a prospective cohort in the region of Augsburg designed to understand the role of genetic, lifestyle, and environmental factors in disease progression including metabolic diseases) that specific microbiota members show 24-hour oscillations in their relative abundance and identified 13 taxa with disrupted rhythmicity in type 2 diabetes. Tang et al^[40]^ identified a microbiome signature containing 21 OTUs that can potentially predict postoperative Hirschsprung-associated enterocolitis with ∼85% accuracy.

The overarching objective of this study is to establish a predicting and monitoring system for EN intolerance in ICU patients based on gut microbiota. Focusing on the relationship between gut microbiota and the host intestinal environment, this project will study the structure and composition of gut microbiota in ICU patients using 16S rRNA sequencing technology, taking patients with trauma and postoperative acute stress as the research subjects. The results of this study will help us to find out the potential probiotics as dietary supplements to improve EN intolerance. The limitation of this study is the single-center design, which may potentially cause recruitment biases.

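### The prognostic analysis does not limit candidate predictors to values recorded before EN intolerance, so later swabs, drugs and feeding data may be reported as predictors when they are consequences

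*Protocol article*

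**What the plan says.** The protocol article gives prediction as an aim. Section 2.1 wants to "screen microbiological markers for predicting EN intolerance in ICU patients", and the Discussion wants to "establish a predicting and monitoring system for EN intolerance". Section 2.1 also has a separate aim, to observe what EN does to the microbiota.

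- **Swabs (2.5.1):** "Fecal samples will be collected on admission and days 3 and 7". A day-14 swab is added only for ICU stays longer than 14 days. Prior EN is an exclusion (2.3), so the admission swab comes before feeding.
- **Clinical data (2.4):** taken from the health record over the whole ICU stay. The drugs in 2.4.1 include "prokinetics, gastric mucosal protectors, coagulants, anticoagulants, antibiotics, vasopressors, anti-diarrhea medicine, cathartics, probiotics". The nutrition data in 2.4.2 include "initiate time of EN, feeding amount, response to feeding".
- **Timing of the outcome (Introduction):** in a cited multi-ICU dataset, "clinical symptoms of EN intolerance appeared on average within 3 days", with a range of 1 to 12 days.
- **Use of the data (Abstract, Methods):** microbial and clinical data are combined "to analyze the baseline characteristics and dynamic alterations of gut microbiota along with the incidence of EN intolerance".
- **Analysis (2.9):** log-rank tests and single-variable Cox models, then a multivariable Cox model whose covariates are chosen from the single-variable results and clinical relevance. Species abundance is compared by Kruskal–Wallis. No sampling day, covariate window, landmark or time-dependent covariate is mentioned.

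**The concern.** A predictor has to be known before the event it predicts. Log-rank tests and an ordinary Cox model treat group membership and covariate values as known at time zero. If a day-7 swab, or a drug first given on day 5, enters such an analysis for a patient whose intolerance began on day 3, the model conditions on the future. The association then runs from outcome to marker. A patient must also still be in the ICU to supply a later value, which adds selection and immortal time.

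Some of the recorded items are plausible reactions to intolerance, for example prokinetics, anti-diarrhoeal drugs and a reduced feeding amount. Response to feeding is close to the outcome itself. Selecting covariates on single-variable association favours just such variables, because a consequence of the event is often its strongest correlate. What is at stake is the predictive aim: a marker list built partly on post-onset values could not be used before onset.

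**Working it through.** **Inputs from the protocol article.** Swabs at admission, day 3, day 7 and (long stays) day 14, from 2.5.1. Onset on average within 3 days, range 1–12, from the Introduction. Intolerance rate 57% and 89 evaluable patients, from 2.8.

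**The plan's own figure.** The 89 reproduces as a one-sample test of 40% against a fixed 57%, two-sided 5%, power 90%:
n = [(1.96·√(0.57·0.43) + 1.2816·√(0.40·0.60)) / 0.17]² = 88.4, rounded up to 89; 89/0.9 = 98.9, stated as about 100. It is used here only to count events: 0.57 × 89 = 50.7, about 51.

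**Assumptions (not in the documents).** Onset is counted from EN start and follows a gamma distribution with shape 1, 2 or 4; the 3-day average is read as either a mean or a median; EN starts L = 0, 1, 2 or 3 days after admission.

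**Share of onsets before a swab on day d** = F(d − L), with F the onset distribution function. For shape 1 and mean 3, L = 0: F(3) = 1 − e^(−1) = 0.632 and F(7) = 1 − e^(−7/3) = 0.903. Across all shapes and both readings:

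| EN start after admission | Before day-3 swab | Before day-7 swab |
|---|---|---|
| 0 days | 50–63% | 80–98% |
| 1 day | 23–49% | 75–96% |
| 2 days | 4–28% | 69–90% |
| 3 days | 0% | 60–78% |

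The share before the admission swab is 0%. For day 14, if EN starts by day 2, the cited maximum gives 2 + 12 = 14, so every onset falls on or before that swab.

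**Events left if only pre-onset samples are used.**
- Admission swab: all of about 51.
- Day 3: from 50.7 × (1 − 0.632) = 19 up to 51.
- Day 7: from 50.7 × (1 − 0.983) = 1 up to 50.7 × (1 − 0.603) = 20.

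**What ignoring the timing can do.** In a simulation (n = 89, 57% intolerant, gamma shape 2 with mean 3 days, L = 0 to 2, 4,000 runs per setting), a normally distributed marker has no predictive value but shifts once intolerance has begun. Ever-intolerant and tolerant patients are compared by Kruskal–Wallis at P < 0.05. Share of runs declaring the marker significant:

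| Shift after onset (assumed) | Admission | Day 3 | Day 7 |
|---|---|---|---|
| none | 4–5% | about 5% | about 5% |
| 0.5 SD | about 5% | 6–26% | 48–57% |
| 0.8 SD | about 5% | 7–54% | 84–92% |

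The admission swab stays at the nominal level. The day-7 swab does not, in any setting with a shift.

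**The case against.** The strongest reply is that section 2.9 does not prescribe the error. It names no candidate variable, does not say whether covariates are fixed or time-dependent, and does not say which groups or days the Kruskal–Wallis test compares. Sections 2.4.1 and 2.4.2 are data-collection lists; 2.4.1 also holds mortality and length of stay, which nobody would take for Cox predictors. Covariate windows and landmarks are often left to an analysis plan. The later swabs have legitimate uses: observing the effect of EN, and monitoring.

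Much of this stands and limits the point. A reader might infer three stronger things that the article does not support.

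- **That the predictive material as a whole is collected after onset.** It is not: the admission swab precedes EN, and the Abstract announces a baseline analysis.
- **That intolerance has usually begun by day 3.** This depends on when EN starts, which the protocol does not fix. The 3-day figure also comes from an outside cohort, and its clock origin is not stated.
- **That consequences will be reported as predictors.** The text permits this; it does not require it.

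The reply does not remove the point. Section 2.9 goes beyond silence: it fixes the methods and a selection rule based on association, applied to data with no cut at onset. The Abstract ties the dynamic microbiota data to the incidence of intolerance. Followed as written, the plan lets post-onset values be selected.

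**Conclusion.** The point holds as a gap in the stated analysis. Nothing in section 2.9 keeps values recorded after intolerance out of the predictor screen or the taxa comparison. The exposure is large for the day-7 swab (about 60–98% of onsets precede it) and for the day-14 swab, and uncertain for day 3 (0–63%). For drugs and feeding data the article gives no basis for a figure, but the direction of the bias is the same.

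These ranges rest on the cited onset figure applying in this ICU, on gamma-shaped onset times counted from EN start, and on EN starting 0–3 days after admission. The false-predictor rates rest further on assumed post-onset shifts of 0.5 or 0.8 SD and are illustrations, not forecasts. The sampling schedule is not at fault and no sample is wasted. The analysis rule needs to change before the data are analysed, because the predictive aim cannot be credibly answered without it.

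**What to change.** Amend section 2.9 as follows.

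1. Base the prediction analysis on the admission swab, confirmed as taken before the first feed, and on clinical covariates recorded before EN start.
2. Start the Cox clock at EN initiation, which 2.4.2 already records.
3. Use the day-3, day-7 and day-14 swabs, drugs and feeding data for prediction only in landmark analyses of patients still free of intolerance at that time, or as time-dependent covariates lagged to before onset.
4. Report all other comparisons of later samples descriptively, under the effect-of-EN and monitoring aims.

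This changes analysis wording only; no new samples or data items are needed. The cost is fewer events in the landmark analyses: under the assumptions above, about 19–51 at day 3 and about 1–20 at day 7, so a day-7 landmark may be too thin to support a model. The admission-swab analysis keeps all of about 51 expected events (57% of 89).

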#### Fecal microbial DNA extraction and sequencing

2.5.2

Microbial DNA will be extracted using an OMEGA-soil DNA Kit (Omega Bio-tek, Norcross, GA). The V1–V3 regions of the 16S rRNA gene will be amplified by polymerase chain reaction with specific primers. After purified and quantified, the amplicons will be pooled and paired-end sequenced on an Illumina MiSeq platform (Illumina, San Diego, CA).

#### 16S rRNA sequence analysis

2.5.3

Operational taxonomic units (OTUs) will be clustered with a 97% similarity cutoff using UPARSE (a method for generating clusters from next-generation sequencing reads of marker genes, http://drive5.com/uparse/), and chimeric sequences will be identified and removed using UCHIME (an algorithm for detecting chimeric sequences, https://www.drive5.com/usearch/manual/uchime_algo.html). The taxonomy of the 16S rRNA gene sequence will be analyzed by RDP (Ribosomal Database Project) Classifier against the SILVA database (a web resource providing comprehensive, quality checked and regularly updated datasets of aligned small (16S/18S, SSU) and large subunit (23S/28S, LSU) ribosomal RNA (rRNA) sequences for all three domains of life (Bacteria, Archaea and Eukarya), https://www.arb-silva.de/). The alpha diversity will be calculated using Chao1, Shannon, and PD (Phylogenetic diversity) indexes based on the OTU profiles to estimate the richness and diversity of the samples. The weighted principal coordinate analysis will be performed based on UniFrac distances to measure community clustering.

### Patient and public involvement

2.6

Patients and the general public were not involved in the design, enrollment, or implementation of the study. Patient care does not differ from the one usually carried out according to the recommendations. Study participants will be able to find the results of the study in scientific publications or conference presentations. They will not be directly informed.

### Adverse outcomes

2.7

During the study, the researchers will ask about adverse events which may be related to the trial. If any adverse events occur, they will be noted in report form and reported in the publication.

### Estimation of sample size

2.8

According to the preliminary survey results, the current EN intolerance rate in the ICU of Beijing Tiantan Hospital is 57%. It is expected that the EN intolerance rate will decrease to 40% after adjusting the EN feeding scheme according to the composition of intestinal flora. The 2-sided type I error rate is 5%, and the power is 90%. In consideration of 10% attrition, the final sample size is ∼100 (89/0.9) cases.

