### Study design and setting

2.2

The study protocol is designed to adhere to The SPIRIT (Standard Protocol Items: Recommendations for Interventional Trials) 2013 Statement.^[33]^ The present trial is a prospective cohort study conducted in a high-volume integrated ICU at the Beijing Tiantan Hospital, Capital Medical University, China. This study protocol was reviewed and approved by the Institutional Review Board of Beijing Tiantan Hospital, Capital Medical University (KY 2019-077-03). The study has been registered in the Chinese Clinical Trial Registry with the registration number ChiCTR2000031760. All eligible patients will be systematically proposed to participate in the study. After written informed consent has been obtained, patients will be enrolled. A flow diagram of this study is shown in Figure 1, and the schedule of the enrollment and assessments according to SPIRIT requirements is shown in Figure 2.

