### Statistical analysis

2.9

The continuous data will be presented as mean ± standard deviation or median (interquartile interval) according to a statistical distribution. The normality will be studied by the Shapiro–Wilk test. The categorical variables will be presented with the number of patients and percentages. To determine prognostic factors for EN intolerance, we will start by univariate analyses using the log-rank test for categorical variables and by the Cox model for continuous parameters. Then, a multivariable analysis will be performed using the Cox proportional-hazards model. The covariates will be determined according to univariate results and their clinical relevance. Kruskal–Wallis rank-sum test will be used to compare species abundance in the gut microbiota data. All tests are bilateral, and *P* < .05 is considered statistically significant. Data related to the gut microbiota will be statistically analyzed by R software, and other data performed by SPSS23.0 (SPSS, Inc, Chicago, IL) software.

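### The 90% power in section 2.8 rests on a flora-guided feeding effect that the described usual-care cohort does not deliver, and it is not tied to any analysis in section 2.9

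*Protocol article*

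**What the plan says.** Section 2.8 (Estimation of sample size) starts from a preliminary survey in which "the current EN intolerance rate in the ICU of Beijing Tiantan Hospital is 57" per cent. It then expects that "the EN intolerance rate will decrease to 40% after adjusting the EN feeding scheme according to the composition of intestinal flora". The error rates follow: "The 2-sided type I error rate is 5%, and the power is 90" per cent. The result is given as: "In consideration of 10% attrition, the final sample size is ∼100 (89/0.9) cases". No test or formula is named.

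The rest of the article describes a different kind of study:

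- Section 2.1 limits the aim to observing how EN affects the gut microbiota and to screening markers that predict intolerance.
- Section 2.2 states: "The present trial is a prospective cohort study conducted in a high-volume integrated ICU".
- Section 2.6 states: "Patient care does not differ from the one usually carried out according to the recommendations".
- Section 2.9 sets out the analysis: "To determine prognostic factors for EN intolerance, we will start by univariate analyses using the log-rank test for categorical variables", with a univariate Cox model for continuous variables, then a multivariable Cox model, and a Kruskal-Wallis test for species abundance. The significance threshold is P < .05.

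**The concern.** The calculation is about a change in the intolerance rate caused by a change in feeding. The study as described changes nothing in care, so it gives no reason for the rate to fall from 57% to 40%. The analysis section contains no test of that fall either.

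Two things are at stake. First, readers are told that the study has 90% power when that figure belongs to a hypothesis the study does not test. They learn nothing about what size of marker effect about 100 patients can detect, and marker screening is the stated aim. Second, the section leaves a historical rate of 57% in the protocol as a benchmark. An observed rate below it could later be taken as a benefit although care was not altered.

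**Working it through.** **Inputs.** From section 2.8: reference rate p0 = 0.57, expected rate p1 = 0.40, two-sided alpha 0.05 (z = 1.960), power 90% (z = 1.2816), attrition 10%. From the Introduction: 30.5% feeding interruption due to intolerance in an international ICU series. From the Discussion: more than 60% of ICU patients forced to discontinue EN.

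**Step 1: reproduce the 89.** One-sample test of a proportion against a fixed value:

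n = [(1.960 × √(0.57 × 0.43) + 1.2816 × √(0.40 × 0.60)) / 0.17]² = [(0.970 + 0.628) / 0.17]² = 88.4, rounded up to 89.

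Attrition: 89 / 0.9 = 98.9, stated as about 100. The arithmetic is right. With 89 patients, power is 90.2% by the normal approximation and 89.8% by the exact binomial (reject if 41 or fewer are intolerant). By contrast, comparing 57% with 40% in two independent groups would need 180 per group, so 89 was not obtained that way.

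**Step 2: look for that test in the plan.** Section 2.9 lists log-rank, Cox and Kruskal-Wallis procedures. None compares the cohort's intolerance rate with 57%, with an earlier period or with a control group. The 90% in section 2.8 therefore belongs to a test that is not listed.

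**Step 3: what 89 patients offer the planned Cox analysis.** The article gives no target hazard ratio (HR) or marker prevalence, so these are illustrations. Expected events at 57%: 0.57 × 89 = 50.7. Using Schoenfeld's formula for one test at two-sided alpha 0.05 with 90% power (1.960 + 1.2816 = 3.2415):

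- Continuous marker, per SD: HR = exp(3.2415 / √50.7) = 1.58.
- Binary marker split 50/50: HR = exp(2 × 3.2415 / √50.7) = 2.48.

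For the 50/50 binary marker with 51 events, power is 30% at HR 1.5, 70% at HR 2.0 and 90% at HR 2.5. Reaching 90% would need 88 events for HR 2.0 and 256 for HR 1.5.

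**Step 4: sensitivity to the event rate.** Detectable HR at 90% power, one test at alpha 0.05:

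| Intolerance rate | Events of 89 | HR per SD | HR, 50/50 binary |
|---|---|---|---|
| 30.5% | 27.1 | 1.86 | 3.47 |
| 57% | 50.7 | 1.58 | 2.48 |
| 60% | 53.4 | 1.56 | 2.43 |

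**Step 5: sensitivity to screening.** The article gives no number of taxa. Assume 20 or 200 Bonferroni-adjusted tests, each by a Cox model with 50.7 events:

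- 20 tests: z = 3.023, sum 4.305. HR = exp(4.305 / √50.7) = 1.83 per SD, or 3.35 binary.
- 200 tests: z = 3.662, sum 4.944. HR = exp(4.944 / √50.7) = 2.00 per SD, or 4.01 binary.

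These show direction and scale only. Section 2.9 does not say that taxa enter the Cox model one at a time, and it assigns species abundance to the Kruskal-Wallis test.

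**The case against.** It can fairly be said that the arithmetic is correct, that about 100 patients is a reasonable size for an exploratory marker study, and that the flora-guided strategy may be a later step, since the Conclusions in the abstract present a new nutrition strategy as something the results will lead to. All of that may be so. But it confirms that the assumed fall to 40% lies outside the study described, and section 2.8 still uses it to claim 90% power. Condensing a full protocol into an article does not explain it, because the premise and the usual-care statement are both printed.

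Several stronger readings do not stand:

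- A reader might infer that no planned analysis reaches 90% power. Step 3 shows otherwise: a single marker with an HR of about 1.58 per SD, or about 2.5 if binary and evenly split, would reach it. What can be said is that the article neither names such a target nor links the 90% to it.
- A reader might treat the one-sample test as stated, or as the only possible source of 89. It is neither. A paired comparison with an assumed 25.5% of discordant pairs gives [(1.960 × √0.255 + 1.2816 × √(0.255 − 0.17²)) / 0.17]² = 88.5, also 89. The one-sample test is simply the most likely source, because it needs no further assumption.
- A reader might infer that the authors plan a before-and-after claim. Neither section 2.1 nor section 2.9 contains one. It is a possible misreading of the results.
- The 30.5% rate should not be taken as the expected event rate here. It describes feeding interruption across many ICUs, whereas the centre's own survey gives 57% and the Discussion mentions more than 60%.

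**Conclusion.** The point holds in this form: section 2.8 is wrong as written because its stated 90% power is for a fall in intolerance after a feeding change that sections 2.1, 2.2 and 2.6 do not include, and section 2.9 does not test that fall. The internal contradiction needs no assumption. That the calculation was a one-sample test against a fixed 57% is an inference from the match at 88.4.

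The sizes in steps 3 to 5 rest on 89 evaluable patients, the assumed event rates, Schoenfeld's approximation and a chosen marker distribution. They show what the sample can and cannot do, and are not corrected figures for the plan. The harm is a misleading justification of the sample size. The finding does not show that 100 patients is the wrong number or that the planned estimates are biased.

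**What to change.** First reconcile section 2.8 with sections 2.2, 2.6 and 2.9, so that the article says consistently whether feeding is adjusted to the flora within this study. Which of the two is intended is for the investigators to state.

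If the study is observational as described:

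- Keep about 100 patients. Remove the 57%-to-40% premise and the 90% power claim.
- Either state that the number is pragmatic, or state what it can detect in the planned analyses. For example: with 89 evaluable patients and an assumed 57% intolerance (about 51 events), a single test at two-sided 5% has 90% power for an HR of about 1.58 per SD, or about 2.5 for an evenly split binary marker.
- Add that larger effects are needed once screening of many taxa is allowed for, and give the assumed number of taxa.
- State that the observed intolerance rate will not be read as an effect against the historical 57%.

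In that case the cost is one rewritten paragraph and no extra patients. The stated power becomes less favourable.
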